### 2.11. Efficacy Assessment

#### 2.11.1. Primary Outcome

The primary outcome will be assessed based on the change in the HB-M score from baseline to 8 weeks. The total HB-M score of subjects who received at least one intervention and for whom a score was measured at least once before the trial or after the intervention will be subjected to analysis. If there is a missing HB-M score, after diagnosing the amount and mechanism of missing values, FAS analysis will be performed by selecting an appropriate imputation method. The change in the HB-M score between the two groups will be verified using an independent t-test. We will use analysis of covariance (ANCOVA) if there is a significant difference in the baseline, and multiple regression analysis if there is a significant difference in the other underlying variables.

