## Abstract

Background: Hwa-Byung is a culturally bound syndrome prevalent in Korea, characterized by intense emotional distress and physical symptoms related to suppressed anger. Patients frequently report experiencing chest tightness, heat sensations, and globus pharyngeus (the sensation of a lump in the throat). These physical symptoms often accompany psychological distress and can exacerbate the sense of frustration and helplessness associated with the condition. The distinctive presentation of these symptoms highlights the necessity for therapeutic interventions that address both the emotional and physical aspects of Hwa-Byung. Conventional therapeutic methods, such as Emotion-to-Emotion Therapy (ETE), have shown efficacy in treating this condition. This study aims to assess the efficacy of Virtual Reality-based Emotion-to-Emotion Therapy (VR-based ETE) compared to conventional ETE, utilizing immersive digital platforms to enhance therapeutic engagement. Methods: This single-center, randomized, assessor-blind, parallel-group clinical trial will enroll 96 participants, evenly divided into two experimental groups and one control group. Over eight weeks, each participant will undergo 12 intervention sessions. Experimental group 1 will receive conventional ETE, experimental group 2 will receive VR-based ETE, and the control group will receive Hwa-Byung management training materials. The primary outcome will be the change in symptoms, measured by the Likert Scale for Major Symptoms of Hwa-Byung from baseline to 8 weeks. Secondary outcomes will include psychometric scales and physiological measures such as the core seven-emotions inventory short form, physical health questionnaire, stress response index, Beck depression inventory, state-trait anger expression inventory, state-trait anxiety inventory, functional near-infrared spectroscopy, and heart rate variability. For economic efficiency assessment, quality-adjusted life-years will be the primary outcome using the EuroQol-5 dimension, and the secondary outcome will be using the EuroQol visual analog scale. Discussion: ETE is a recognized oriental psychotherapy that enhances symptom management, self-regulation, and stress coping. VR is expected to deepen treatment immersion. By combining these strengths, VR-ETE may further improve emotion regulation and alleviate psychosomatic symptoms. If successful, this study will not only advance the treatment of Hwa-Byung but also contribute to the modernization of traditional Korean medicine through the integration of digital therapies.

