#### 2.4.3. Sample Size

The statistical hypothesis test of the evaluation variable is two-sided, and the significance level will be set at 5%. The type 2 error (β) will be set to 0.2, and the power will be maintained at 80%. The ratio of the experimental 1, experimental 2, and control groups should be 1:1:1. We expect the HB-M reduction in the control group and experimental group to be 2.52 and 6.84, respectively, and pooled standard deviation 5.178 based on previous studies conducted with a design similar to this study [37]. Therefore, the required sample size for each group is expected to be “2 × 6.9^2^ × (1.96 + 0.84)^2^/(7.8 − 2.8)2 ≃ 30/group ”. In addition, considering a dropout rate of 25%, we decided to register 32 participants per group, for a total of 96 participants.

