#### 2.4.4. Randomization and Blinding

The people in charge of other assignments (or independent statisticians) who are not involved in conducting and evaluating this clinical trial will generate a random assignment list in a specific and reproducible manner. Randomization of experimental group 1, group 2, and the control group will be performed with a block randomization method in a 1:1:1 ratio. The random assignment table will be sealed and kept in a way that can be checked for unsealing, managed separately by the research manager in the presence of the participants. Each group will be randomly assigned with the same probability of each individual being selected using the statistical program StataMP 16 program (StataCorp LLC, [name]). The investigators and assessors will be separated so that the assessors will not know what kind of treatment the subjects have received. It is not possible to maintain investigator blindness.

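### The primary t-test compares two unnamed groups in a three-arm trial, and the stated aim and the sample-size basis point to different pairs

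*Protocol article*

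**What the plan says.** The Abstract describes 96 participants "evenly divided into two experimental groups and one control group", and section 2.4.4 confirms it: "Randomization of experimental group 1, group 2, and the control group will be performed with a block randomization method in a 1:1:1 ratio".

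Section 2.11.1 defines the endpoint: "The primary outcome will be assessed based on the change in the HB-M score from baseline to 8 weeks". It then gives the test: "The change in the HB-M score between the two groups will be verified using an independent t-test". If groups differ at baseline, the same section switches to ANCOVA or multiple regression, again without naming a contrast.

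Two other places bear on which pair is meant:

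- **Aim** (Abstract, end of the Introduction, Discussion): VR-based ETE compared with conventional ETE.
- **Sample size** (section 2.4.3): an expected HB-M reduction of 2.52 in the control group and 6.84 in a single experimental group, with no statement of which experimental arm. The error rate is set once: "The statistical hypothesis test of the evaluation variable is two-sided, and the significance level will be set at 5"%. Power is 80%.

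ANOVA appears only among the optional safety tests in section 2.12.

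**The concern.** Three arms give three possible pairs, and a two-sample t-test uses one of them. The primary rule has to say which pair decides the trial, and this one does not. The rest of the article does not settle it, because its two cues conflict: the aim implies VR-based ETE against conventional ETE, and the sample size implies control against an active arm.

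The choice of pair can change the answer. Suppose both active arms beat control by the same planned amount. A test of either active arm against control would usually be significant, while a test of VR-based against conventional ETE would be non-significant about 95% of the time. Both analysts would have followed section 2.11.1. A positive primary result could also come from conventional ETE against control, which says nothing about VR.

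An unnamed pair also leaves room for testing several pairs at 5% each and counting any success.

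**Working it through.** **1. The plan's own figure.** Section 2.4.3 prints a two-group formula with SD 6.9 and difference 7.8 − 2.8 = 5.0:

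2 × 6.9² × (1.96 + 0.84)² / 5.0² = 29.86, so 30 per group. The stated figure reproduces.

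The prose inputs in the same section differ: difference 6.84 − 2.52 = 4.32, SD 5.178. They give 2 × 5.178² × 2.8² / 4.32² = 22.5, so 23 per group (24 by exact t-test power). That mismatch is a separate matter, so both sets are carried below. Either way the calculation is for one two-group comparison at an unadjusted 5%.

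**2. Evaluable number.** 32 per group less 25% dropout: 32 × 0.75 = 24 per arm.

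**3. Cues side by side.**

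| Place | Pair implied |
|---|---|
| Abstract, Introduction, Discussion (aim) | VR-based ETE vs conventional ETE |
| 2.4.3 (sample size) | control vs one experimental arm, not named |
| 2.11.1 (primary test) | two groups, not named |
| 2.11.1 (ANCOVA or regression fallback) | none named |

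**4. Conditional error rate.** Assume no true differences, equal arms, unadjusted two-sided 5% tests, and success if any test is significant.

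- Two tests sharing an arm (correlation 0.5): 1 − P(|Z₁| ≤ 1.96 and |Z₂| ≤ 1.96) = 9.1%.
- All three pairs: P(range of three standard normals > 1.96 × √2) = 12.2%.
- Simulation of t-tests at 24 per arm agrees: 9.0% and 12.2%.
- One named pair: 5%.
- Overall F-test at 5%, then pairs at 5% only if F is significant: about 5% (simulated 4.9%).

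These rates do not depend on the effect size or SD.

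**5. Power for an active arm against control, 24 per arm.** Unadjusted t-test, compared with the same test counted only when the overall F-test is significant:

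| Inputs | Standardised difference | Unadjusted | Gated, both active arms equal | Gated, other active arm has half the effect |
|---|---|---|---|---|
| Prose | 4.32/5.178 = 0.834 | 81% | 77% | 71% |
| Printed formula | 5.0/6.9 = 0.725 | 69% | 63% | 57% |

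The loss is about 4 or 10 points with the prose inputs, and about 6 or 12 with the formula inputs.

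**6. Can baseline adjustment recover this?** Assume equal SDs at baseline and week 8 and correlation ρ. The ANCOVA variance is then (1 − ρ²)/[2(1 − ρ)] = (1 + ρ)/2 of the change-score variance. At standardised difference 0.834 with equal active arms, gated power is about 88% at ρ = 0.5, 81% at ρ = 0.8 and 79% at ρ = 0.9, against 81% for the ungated t-test. The article gives no ρ.

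**The case against.** The strongest reply is that section 2.11.1 states a single t-test. Nothing says that it will be repeated over pairs or that success on any pair counts. With one contrast, a fixed sequence, or a rule that every contrast must succeed, the error stays at or below 5%. This stands. A reader might infer that the trial runs at a 9% to 12% false-positive rate, but the text does not support that. Those figures describe what the wording would allow.

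A second reply is that this is a journal article, and that test order and alpha allocation normally sit in the full protocol or the SAP, neither of which is shown. This also stands: the absence of a multiplicity scheme here is not a finding. It does not excuse the sentence itself, which fixes a method and describes a three-arm design as two groups. Condensation does not explain it either, since the section finds room for two fallback models.

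A third reply is that the intended pair can be worked out from context. It cannot, because the aim and the sample-size basis give different answers.

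**Conclusion.** The point holds as a defect in the primary rule. The deciding contrast is not named, and the article's two cues to it disagree. That conclusion needs no numerical assumption.

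The family-wise error of about 9% (two comparisons sharing an arm) or 12% (all three pairs) is conditional on each test being run at 5% with any success counting. The stronger claim, that the plan inflates the error, goes beyond the document.

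The power figures assume 24 evaluable per arm and one or other of the two input sets in section 2.4.3, which disagree. The correction should be made before outcomes are seen, because a pair chosen afterwards cannot be defended.

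**What to change.** Replace the reference to two groups in section 2.11.1, and in its ANCOVA and regression fallback, with named contrasts. Either route is sound:

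**(a) One primary contrast.** Name it, test it at two-sided 5%, and make the others secondary or test them in a fixed sequence. For a named active arm against control this costs no power and leaves the sample size as it is, but the aim should then be worded to match. If VR-based against conventional ETE is chosen, section 2.4.3 needs an expected difference for that pair, which it does not give. As an illustration only, half the prose difference would need four times the number: 4 × 22.5 ≈ 90 per group before dropout.

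**(b) All three pairs, if they matter equally.** Fit one model with a three-level arm factor. Test the overall 2-df arm effect at 5%, and test each pair at 5% only if the overall test is significant. With exactly three arms this is a closed procedure and holds the family-wise error at 5%. It costs about 4 to 10 points of power per active-against-control contrast with the prose inputs, or 6 to 12 with the printed-formula inputs. Bonferroni over three tests would leave 66% (prose inputs), compared with 71% to 77% here. Adjusting for baseline HB-M may recover some or all of the loss, depending on the unstated correlation.

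Both routes change wording only, apart from the extra sizing work if VR-based against conventional ETE becomes primary.

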### 2.10. Statistical Analysis

Efficacy analysis will be evaluated primarily based on the Full Analysis Set (FAS) principle and secondarily according to the Per-Protocol (PP) principle of the primary outcome. Missing values will be imputed appropriately according to why they occur. Subjects are excluded from FAS analysis in following cases: failure to meet eligible criteria, no intervention specified in the clinical study plan has been received, no data have been collected because they have never been evaluated since randomization. Subjects will be excluded from the per-protocol (PP) analysis if they meet any of the following conditions: 1. Dropped out during the trial. 2. Violated the inclusion or exclusion criteria. 3. Had less than 75% compliance with the overall intervention. Additionally, other serious violations of the study protocol may also be considered as grounds for exclusion from the PP analysis. The demographic data of the study subjects included in this trial and baseline clinical history data will be presented with mean and standard deviation (SD) for continuous data for each group and frequency and percentage for categorical data. For each group, an independent sample t-test or Wilcoxon rank sum test will be performed depending on normality in the case of continuous variables, and for categorical variables, a Pearson chi-square test or Fisher’s practice test will be performed.

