#### 2.11.2. Secondary Outcome

The secondary outcome will be assessed by changes in the HB-M score from baseline to 16 weeks, changes in the CSEI-S, PHQ-15, SRI, BDI, STAXI, and STAI from baseline to 8 and 16 weeks, and changes in the fNIRS and HRV from baseline to 8 weeks.

CSEI-S measures the core emotions of the patient in a clinical setting [38]. PHQ-15 assesses depression and physical symptoms [39]. SRI measures the degree of stress response [40]. BDI measures the current severity of depression, regardless of psychiatric diagnosis [41]. STAXI measures anger experiences and forms of anger expression [42]. STAI measures state anxiety and trait anxiety [43]. fNIRS shows prefrontal cortex activation which is prominent during both emotional processing and regulation [44]. HRV measures heart rate variability consistent with autonomic nervous system functional status [45].

We will use ANCOVA or baseline-variables-corrected multiple regression analysis for the efficacy assessment of the CSEI-S, PHQ-15, SRI, BDI, STAXI, STAI, fNIRS, and HRV variables. The baseline score will be used as a covariate, in which case a PP analysis will be performed without handling missing values.

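### The primary HB-M analysis adjusts for baseline only after a significant baseline difference, so chance chooses the model and free precision is lost

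*Protocol article*

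**What the plan says.** The primary outcome is the change in HB-M from baseline to 8 weeks (protocol article, section 2.11.1). Its default test is an independent t-test on that change. Two conditions can replace the default:

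- "We will use analysis of covariance (ANCOVA) if there is a significant difference in the baseline"
- "multiple regression analysis if there is a significant difference in the other underlying variables"

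Section 2.10 plans significance tests between groups on baseline data: "For each group, an independent sample t-test or Wilcoxon rank sum test will be performed depending on normality", with chi-square or Fisher tests for categorical variables. The article does not say outright that these tests feed the triggers, but they are the only baseline tests it describes.

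Section 2.11.2 treats the listed secondary measures (CSEI-S, PHQ-15, SRI, BDI, STAXI, STAI, fNIRS, HRV) differently. There, "The baseline score will be used as a covariate", with no significance condition. No section fixes ANCOVA as the primary model whatever the baseline comparison shows.

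**The concern.** Allocation is random, so a baseline difference between arms is a chance event. Its p-value does not show whether baseline HB-M predicts week-8 HB-M, and that prediction is what makes adjustment worthwhile. Three consequences follow.

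1. **Precision.** Most trials run under this rule would report the unadjusted change score, although a more precise estimate is available from data already collected.
2. **Conditional bias.** The change score over-corrects for baseline: an arm that starts higher by chance tends to fall further by regression to the mean. A gap that just misses significance is left in the estimate.
3. **Model choice.** The headline result may come from a t-test, an ANCOVA or a multiple regression whose covariates are not named, and the choice is made after data are seen. With three arms, different pairs could be analysed by different models.

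**Working it through.** **Inputs.** Two-sided alpha 0.05, 80% power, 1:1:1 allocation, 25% dropout and 32 per group registered (section 2.4.3). The prose there gives "HB-M reduction in the control group and experimental group to be 2.52 and 6.84, respectively, and pooled standard deviation 5.178", a difference of 6.84 − 2.52 = 4.32. The printed formula uses other values: "2 × 6.9^2^ × (1.96 + 0.84)^2^/(7.8 − 2.8)2 ≃ 30/group".

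**The plan's own figure.** The formula gives 2 × 6.9² × 2.8² / 5² = 29.86, so 30 per group reproduces. The prose inputs give 22.55, so 23 per group by the normal approximation, or 24 by the exact t-test. Only the latter leads to the registered number: 24 / 0.75 = 32. The prose inputs are therefore used below, with 24 per arm after dropout and 5.178 read as the SD of change.

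**Assumed.** The baseline to week-8 correlation (rho) is not given; 0.3, 0.5 and 0.7 are shown. SDs are taken as equal at the two times.

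**Variance.** With common SD s, the change score has variance 2s²(1 − rho) and the ANCOVA residual has s²(1 − rho²). The ratio is (1 + rho)/2 = 0.65, 0.75, 0.85. The required number per group falls from 23 to 15, 17 and 20 (22.55 × 0.65 = 14.7; × 0.75 = 16.9; × 0.85 = 19.2).

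**Simulation** (200,000 two-arm trials per setting, difference 4.32, SD of change 5.178):

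| | rho 0.3 | rho 0.5 | rho 0.7 |
|---|---|---|---|
| Power, t-test on change, 24 per arm | 81% | 81% | 81% |
| Power, conditional rule, 24 per arm | 82% | 82% | 81% |
| Power, always ANCOVA, 24 per arm | 93% | 90% | 86% |
| Power, conditional rule, 32 per arm | 92% | 92% | 91% |
| Power, always ANCOVA, 32 per arm | 98% | 96% | 94% |
| Type I error, conditional rule, 24 per arm | 4.1% | 4.3% | 4.7% |
| Type I error, always ANCOVA, 24 per arm | 4.9% | 5.0% | 5.0% |

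At rho 0.5 and 24 per arm, the standard error of the effect is 1.49 for the t-test, 1.44 for the conditional rule and 1.31 for ANCOVA. The rule recovers little of the available gain.

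**Conditional on the baseline gap.** If the arms differ by d at baseline, the expected difference in change is the true effect minus (1 − rho)d. At rho 0.5 the SD at each time is 5.178, so the standard error of the gap is 5.178 × √(2/24) = 1.49. A non-significant gap of 1.5 standard errors is 2.24 points and shifts the change-score estimate by 0.5 × 2.24 = 1.12 points, about a quarter of 4.32. In simulation, about 27% of trials have a non-significant gap above 1 standard error. Among these the t-test's false-positive rate is 8.1%, 7.4% and 6.5% at rho 0.3, 0.5 and 0.7 (repeat runs agreed within about half a point), while ANCOVA stays near 5%. In the 68% of trials with a gap below 1 standard error it is 2.4%, 3.1% and 3.9%.

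**Switching models.** For baseline HB-M the trigger fires about 5% of the time per comparison. For at least one of three pairwise comparisons the chance is about 1 − 0.95³ = 14%, treating them as independent. If 10 to 20 independent baseline variables were tested, at least one would be significant with probability 1 − 0.95¹⁰ = 40% to 1 − 0.95²⁰ = 64%. The article does not count these tests, so that range is only illustrative. The regression branch was not simulated, because its covariates are not named.

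**The case against.** The strongest reply is that the present rule is valid. Under randomisation the change-score t-test is unbiased on average, and the overall type I error of the conditional rule is slightly below 5%. The raised error in trials with a moderate gap is balanced by a low one in trials with a small gap, and the bias falls equally in both directions. This stands: the bias is conditional, and there is no overall inflation.

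On the prose inputs the rule still gives 81% to 82% power, which meets the 80% target. This also stands: the loss is relative to a better analysis of the same data. The reply is weaker on the formula's inputs (difference 5.0, SD 6.9). With 24 per arm the conditional rule then has about 70% power and ANCOVA about 85% to 75% across rho 0.3 to 0.7.

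The gain depends on an unstated correlation and shrinks as it rises. At 0.8, ANCOVA has 84% against 81%; at 0.9, 81.5% against 80.4%. It remains positive for any correlation below 1 under equal SDs.

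The contrast with the secondary outcomes holds only for the measures listed in section 2.11.2. Week-16 HB-M, also secondary, is not in that list.

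It could also be said that a separate analysis plan may settle the model. But the article states a definite rule for the primary endpoint, and such a plan would have to contradict it.

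**Conclusion.** The concern holds, as a change that should be made rather than a threat to validity. At 24 per arm on the prose inputs, the conditional rule gives up about 11, 8 and 5 points of power at rho 0.3, 0.5 and 0.7 compared with ANCOVA throughout. It also leaves moderate chance imbalances uncorrected and does not fix the primary model before data are seen. These sizes rest on the assumed correlations, on equal SDs at baseline and week 8, and on reading 5.178 as the SD of change. The direction does not depend on which of the two sample-size input sets is used.

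**What to change.** In section 2.11.1, name one primary analysis: a linear model for week-8 HB-M with arm and baseline HB-M as terms, used for every between-arm comparison whatever the baseline data show. Using the change score as the response in that model gives the same treatment effect. Delete both significance triggers. In section 2.10, present baseline data descriptively and drop the significance tests that would feed the triggers. If other covariates are wanted, name them in advance. Keep the unadjusted t-test on change as a sensitivity analysis.

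The cost is about one sentence and one degree of freedom. Baseline HB-M is already collected before the intervention at visit 1, so no new data or participants are needed, and the primary analysis would then match the treatment of the listed secondary measures. The change should be made before outcome data are examined by arm.
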